#### Data collection and follow-up

Investigators will save a recording of the operation and note the procedure time. After EUS-guided drainage, patients will be sent back to the ward. Patients will be monitored for 3 h and 24 h serum amylase after the operation and prophylactic antibiotics will be administered postoperatively. Detailed data information can be found in the SPIRIT figure (Fig. 3). After the LAMS is implanted, if the WON needs to be cleaned, direct endoscopic necrosectomy (DEN) will be performed. Stents will be removed one month after implantation. If the clinical success criterion is not met at the one-month follow-up, the patient will be provided with further treatment that will be decided based on their individual needs. All individuals who participated in the trial will be followed up at one, three, and six months post operation, with a final follow-up to occur 12 months after the end of the trial for CT evaluation. The above data will be collected into case report forms (CRFs). Stent-related AEs and management will also be recorded and reported in the CRFs. Finally, CRFs will be summarized by the National Clinical Research Center for Digestive Diseases.

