**Fig. 3 Fig3:**
[figure not shown]
Schedule of enrollment, follow-up, and assessments. Basline^0^: screening of laboratory tests can be accepted the previous week in our hospital inspection report. Stent removal^1^: time from stenting to postoperative withdrawal (33 ± 3 days). Blood routine^2^: hemoglobin (HGB), erythrocyte count (RBC), platelet count (PLT), leukocyte count (WBC), neutrophil percentage (%), lymphocyte percentage (%). Liver and kidney function^3^: alanine aminotransferase (ALT), aspartate aminotransferase (AST), total bilirubin, direct bilirubin (DBIL), indirect bilirubin (IBIL), alkaline phosphatase (ALP), glutamyl transferase (GGT), blood urea nitrogen (BUN), creatinine (Cr). Coagulation function^4^: prothrombin time (PT), fibrinogen (FIB), activated partial thromboplastin time (APTT), thrombin time (TT). Serum amylase^5^: assessed 3 h and 24 h after the operation. CT^6^: preoperative and postoperative enhanced CT examination, 3 months and 6 months postoperative CT examination. The primary endpoint^7^: immediate success rate of surgery, drainage success rate 1 month after surgery. Secondary endpoints^8^: the incidence of clinical complications, operation time, the recurrence rate of pancreatic pseudocyst within 1 month and 1 month after the operation, and secondary interventions

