#### Outcomes

The primary outcome is the clinical success rate at one month after drainage. Clinical success is defined as reduction in the size of WON to < 2 cm. Within one month of the drainage, if the patient needs to change the treatment method (such as the additional placement of nasal cyst drainage tube; or the DPPS removed and replaced with a LAMS), it will be recorded as drainage failure. The secondary outcome is technical success, operation time, recurrence, AEs, and secondary interventions. The definitions of the primary and secondary outcomes are presented in Table 2.

**Table 2 Tab2:** Definitions of the primary and secondary outcomes

Outcomes	Description
Clinical success	The diameter of the WON ≤ 2 cm
Technical success	LAMS or DPPS deployed successfully
Operation time	Time duration from the beginning to the end of the EUS-guided stent implantation procedure
Recurrence	After successful drainage, cyst reappears on imaging examinations with symptoms requiring intervention
Adverse event	
Perforation	Imaging manifests as pneumoperitoneum with peritoneal irritation syndrome
Bleeding	Any bleeding that requires intervention, blood transfusion, and hospital observation
Suprainfection	Postoperative fever, increased inflammatory index (CRP, PCT), or positive blood culture
Occlusion	The stent is filled with tissue or debris
Migration	The stent is completely or partially displaced into the WON or stomach
Others	Adverse events that occurred in the trial but not described above
Secondary intervention	Any endoscopic operation after stent is placed

*CRP* C-reactive protein, *PCT* procalcitonin

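### The secondary-intervention outcome does not except the scheduled stent removal, so the proportion of patients with an event is near 100% in both arms; non-endoscopic procedures fall outside it

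*Protocol article*

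**What the plan says.** The Outcomes section lists the secondary outcomes: "The secondary outcome is technical success, operation time, recurrence, AEs, and secondary interventions". It then names the place that governs their meaning: "The definitions of the primary and secondary outcomes are presented in Table 2". In Table 2 the entry for secondary intervention reads, in full, "Any endoscopic operation after stent is placed". It has no exception for planned procedures, and its only limit is the endoscopic route.

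Data collection and follow-up states "Stents will be removed one month after implantation", with no condition on arm or response. The Fig. 3 legend gives removal its own schedule entry: "time from stenting to postoperative withdrawal (33 ± 3 days".

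Two further statements in the same section bear on what the outcome captures. On necrosectomy: "After the LAMS is implanted, if the WON needs to be cleaned, direct endoscopic necrosectomy (DEN) will be performed". On patients who have not met the success criterion at one month: "the patient will be provided with further treatment that will be decided based on their individual needs". The second does not restrict the route of treatment.

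**The concern.** A re-intervention outcome should show how often the index drainage was not enough or led to a complication. As worded, a patient who drains well and attends only for routine removal has an event. A patient sent for percutaneous drainage or surgery has no event from that procedure.

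The outcome matters to this trial. The Background cites fewer procedures with LAMS (2.2 versus 3.6) as part of the argument for it, and the Discussion repeats the point. Secondary intervention is the only listed outcome that addresses procedure burden directly. If it is reported as the proportion of patients with any event, a real advantage or disadvantage of LAMS would be almost invisible, and similar percentages could be misread as equivalence.

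**Working it through.** **Background figure.** The article gives no expected rate for secondary interventions, so there is no figure of its own to reproduce for this outcome. Its primary sample size does reproduce. With success rates of 0.90 and 0.75, one-sided alpha 0.025 and power 85%, the stated formula gives

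n = [1.960·√(2·0.825·0.175) + 1.036·√(0.90·0.10 + 0.75·0.25)]² / 0.15² ≈ 113.7, so 114 per arm.

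With 10% dropout, 114/0.90 = 126.7, so 127 per arm and 254 in total, against 256 stated. The only use made of this below is the evaluable number per arm, 128 × 0.9 ≈ 115.

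**Step 1: a bound that needs no assumed re-intervention rate.** Let r be the proportion of patients whose stent is removed endoscopically as scheduled. Each of them has an event under Table 2, so the event proportion in an arm is at least r. If r is at least 90% in both arms, both proportions lie between 90% and 100%, and they cannot differ by more than 100 − 90 = 10 points.

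**Step 2: the expected shrinkage.** Let u be the true proportion with some other re-intervention. If removal is independent of re-intervention and r is the same in both arms:

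- event proportion = 1 − (1 − u)(1 − r)
- difference between arms = (1 − r) × (true difference in u)

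The article gives no values of u, so the following are assumptions. Take u = 30% versus 50%, with 115 per arm and a two-sided 0.05 test (normal approximation, pooled variance under the null hypothesis).

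| Scheduled removal | Event proportions | Difference | Power |
|---|---|---|---|
| Not counted | 30.0% vs 50.0% | 20 points | 88% |
| Counted, r = 90% | 93.0% vs 95.0% | 2 points | 9% |
| Counted, r = 95% | 96.5% vs 97.5% | 1 point | 6% |
| Counted, r = 98% | 98.6% vs 99.0% | 0.4 points | 5% |
| Counted, r = 100% | 100% vs 100% | 0 | no contrast |

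Worked example for the first two rows:

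- Not counted: the null standard error is √(0.40·0.60·2/115) = 0.0646 and the alternative is √((0.21 + 0.25)/115) = 0.0632. Then (0.20 − 1.96·0.0646)/0.0632 ≈ 1.16, which gives 88%.
- Counted at 90%: the standard errors are both about 0.0313. Then (0.02 − 1.96·0.0313)/0.0313 ≈ −1.32, which gives 9%.

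Assumed rates of 20% versus 40% and 40% versus 60% show the same pattern: power of 92% and 86% with removal excluded, and about 4% to 10% with it counted. The approximation is rough when proportions are this close to 100%, so the low power values show scale only.

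**Step 3: the same event in a count.** If the measure is procedures per patient, scheduled removal adds about r, close to one, to each arm's mean, and the difference is unchanged. Using the Background's 2.2 and 3.6 purely as an arithmetic example, adding one gives 3.2 and 4.6, and the difference is 1.4 both times. The ratio moves from 2.2/3.6 = 0.61 to 3.2/4.6 = 0.70.

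**Step 4: which route is counted where.**

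| Place in the article | Route covered |
|---|---|
| Secondary intervention, Table 2 | Endoscopic only |
| Drainage failure within one month (primary outcome) | Any change of treatment method; the examples given are not exhaustive |
| Bleeding and recurrence, Table 2 | Intervention by any route |
| Management of stent-related adverse events | Recorded on the case report form, route not limited |

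**The case against.** The strongest reply is that no one would count a scheduled step of the index treatment as a secondary intervention. The Fig. 3 legend lists stent removal as its own item, apart from the secondary endpoints. Because removal has a defined window, it could be separated at analysis. This makes the intended meaning plausible, but it does not amend Table 2, which says any endoscopic operation and which the article names as the governing definition.

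Second, the article never says in words that removal is endoscopic. That is correct. It is inferred from stents placed endoscopically through the gastric wall. Patients who die, withdraw or lose the stent first would have no removal, so near 100% is the right strength, not 100%.

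Third, a reader might infer that the outcome cannot separate the arms at all. The article does not support that. It does not say whether the measure is a proportion or a count, and on a count the difference survives. The loss of contrast applies to the proportion.

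Fourth, a reader might infer that percutaneous and surgical rescue goes uncounted in the trial. That is also too strong. As Step 4 shows, such a procedure within one month can make the patient a drainage failure in the primary outcome, and bleeding and recurrence do not depend on route. What stands is narrower: these procedures are outside this one endpoint, and no named outcome counts them as interventions in their own right. Limiting the outcome to endoscopic procedures could be a deliberate choice of scope, but the article gives no reason for it.

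Fifth, excluding removal does not by itself settle the outcome. "if the WON needs to be cleaned, direct endoscopic necrosectomy (DEN) will be performed" appears only in connection with LAMS, and such a session is also an endoscopic operation after stent placement. It would still count, possibly unequally between the arms. A definition built on the word unplanned would leave its status open, so the fix has to name it.

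**Conclusion.** The definition is badly fixed and should be corrected; it is not a detail left to a fuller document. Read literally, it makes a step scheduled for every patient an outcome event. The proportion with at least one secondary intervention is then near 100% in both arms, and the true difference is multiplied by about 1 − r: 20 points become 2, 1 or 0.4 points at removal rates of 90%, 95% or 98%. This rests on removal being endoscopic, on similar removal rates in the two arms, on removal being independent of other re-intervention, and on re-intervention rates that are assumed. The 10-point ceiling at 90% removal needs only the first of these and at least that rate in each arm. On a per-patient count, each arm is inflated by about one and the difference is intact.

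The restriction to endoscopic procedures is a separate, smaller gap in the same endpoint, and it affects the proportion and the count alike. Severity is moderate: one secondary outcome is affected, and the primary endpoint and sample size are unchanged.

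**What to change.** Replace the Table 2 entry with a definition along these lines: any endoscopic, percutaneous or surgical procedure for the WON or for a stent complication after the index procedure, excluding the scheduled stent removal. State explicitly that direct endoscopic necrosectomy sessions are counted, and also report them on a separate line by arm, so that a difference caused by necrosectomy can be seen. Say whether the summary is the proportion with at least one procedure, the number per patient, or both.

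On the case report form, record the type of each procedure after the index and whether it was the scheduled removal (yes/no). Settle this before data accrue: in an open-label trial, deciding afterwards which procedures count is open to bias.

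The cost is one table entry and two form fields. It changes what is measured and leaves visits, procedures and patient management as they are.

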#### Statistical considerations

##### Sample size

The sample size calculation is based on a literature review and conference discussion regarding the clinical success rate of LAMS or DPPS drainage for WON. The LVPWON trial is a superiority trial in which the sample size calculation was based on the assumption that the incidence of the primary endpoint with LAMS and DPPS is 90% and 75%, respectively. Assuming a one-side alpha (type I error) of 0.025 and a power of 85% (beta, a type II error, was taken as 0.15), we used the following formula to calculate sample size and found that 256 patients (128 per condition) would be necessary, including a possible dropout rate of 10%.

$$ n={\frac{\mu_{1-\alpha}\sqrt{2\overline{p}\left(1-\overline{p}\right)}+{\mu}_{1-\beta}\sqrt{p_T\left(1-{p}_T\right)+{p}_C\left(1-{p}_C\right)}}{{\left({p}_T-{p}_C\right)}^2}}^2 $$

In this formula, *p*_*T*_ represents expected success rate of the LAMS group, *p*_*C*_ indicates expected success rate of the DPPS group, $$ \overline{p} $$ is average success rate of the two groups, and *μ* represents the quantile of standard normal distribution.

##### Data management

Patient characteristics will be recorded in a CRF. An electronic data collection system (electronic data capture [EDC]) will be used to complete the trial data collection. The EDC system has been rigorously tested to fully meet the requirements of the “Quality Management Practice for Medical Device Clinical Trials” and “Technical Guidelines for Clinical Trial Data Management Work.” Before the system is officially launched, training tests will be conducted on relevant users to ensure that the system meets the trial requirements. After the official launch, related personnel will receive the account number and password. The account is bound to the user’s role and permissions: the user must properly maintain the account information, not inform others about the account information, and exercise appropriate rights for others. Clinical auditors will monitor the clinical trial center’s work at least once a month. This trial has an interim analysis once half of the required number of the patients have been enrolled, during which the data will be analyzed. If a serious AE is identified, the study will be terminated immediately.

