#### Study population

This prospective study will be performed at the National Clinical Research Center for Digestive Diseases and 18 tertiary hospitals in China. All adult patients admitted with WON will be assessed for eligibility during their hospital admission. If patients are found to have solid debris in the PFC and fulfill all inclusion and exclusion criteria, they will be randomized (at a 1:1 ratio) to the LAMS or DPPS group after obtaining signed informed consent (Fig. 1). In this experiment, randomization will be performed using the Interactive Web-Respond System (IWRS).

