##### Statistical analysis plan

Categorical data will be described using frequency and composition ratios. Continuous data will be described using mean, standard deviation, maximum, minimum, and median, as well as 25th and 75th quantiles. Baseline demographic analysis based on the descriptive analysis, the likelihood ratio χ2 test will be used for the comparison between the categorical data groups. Fisher’s exact probability method will be used when theoretical frequency of cells exceeding 25% is < 5. Normally distributed continuous datasets will be compared using a group *t*-test. For non-normally distributed continuous data, Wilcoxon rank sum test will be used for comparison between groups. This is a multi-center study. The test conditions of each center are not identical (such as operators, etc.) and the outcomes may be different. For the primary outcome, comparison between groups will be performed using the CMH (Cochran–Mantel–Haensel) χ2 analysis to adjust for the central effect. The differences between the success rates of the groups and their 95% confidence intervals (CI) will also be estimated. AEs will be described by the number and incidence of AEs; the likelihood ratios between groups will be compared using the χ2 test or Fisher’s exact probability test. Major investigators will have access to the final trial dataset and the statistician involved will be blinded to the treatment assignments. Statistical analysis will be performed with two-sided tests at a level of significance of 0.05 (except where specified). Data analysis will be conducted using SAS^®^9.4 statistical software.

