## Discussion

The LVPWON trial has been designed to answer the question of whether LAMS is superior to DPPS for EUS-guided drainage of WON with regards to the clinical success rate and the incidence of AEs. We also want to prospectively investigate the risk factors for success of treatment and complications of EUS-guided drainage, which will provide a reference for the clinical treatment of WON.

EUS-guided drainage has been maturely applied in late PFC with well-defined inflammatory walls [7, 16–18]. Stents used for drainage are diverse. DPPS used in the management of PFC was first reported in the 1980s [19]. Subsequently, self-expanding metal stents (SEMS) and double-flanged LAMS have become the most popular drainage stents for PFC [8, 11, 12].

Due to their small diameter, several DPPSs are needed to achieve adequate drainage of a WON. Metal stents that have a larger diameter are theoretically considered superior to DPPS as they allow for the possibility of WON debridement. A previous study directly comparing DPPS and LAMS demonstrated that the latter had a success rate of 90%, which was higher than the former, and a significantly fewer number of procedures were required with LAMS for WON resolution [10]. In terms of AEs, stent occlusion seems more likely to occur in WON treated with DPPS [10]. Furthermore, new technology associated with LAMS enhance the drainage effect [20]. The procedure of LAMS deployment has become much easier and more economical.

However, with the increasing use of LAMS for WON drainage, LAMS-related bleeding has been more frequently reported [13–15]. In combined endoscopic and percutaneous drainage for symptomatic WON, LAMS did not reduce the time to percutaneous drain removal and was not associated with fewer AEs [21]. Furthermore, LAMS is substantially more expensive than DPPS.

Recently, a consensus guideline formulated by the Asian EUS group RAND/UCLA expert panel raised the issue of stent selection [5]. There are currently no randomized data addressing how LAMS compare with DPPS for WON drainage. An ongoing RCT observed serious LAMS-related AEs, including delayed bleeding in 50% of patients (6/12), buried stent syndrome, and biliary stricture [14]. However, our team had analyzed our center’s experience and determined that the use of LAMS is safe [22].

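### The written rule that one serious adverse event ends the study conflicts with completing 256 patients, with the planned comparison of adverse events, and with the serious events the article itself cites

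*Protocol article*

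**What the plan says.** In the protocol article, the Data management section plans one look: "This trial has an interim analysis once half of the required number of the patients have been enrolled, during which the data will be analyzed". The next sentence is the only stated consequence: "If a serious AE is identified, the study will be terminated immediately".

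Other sections assume that the trial runs to completion and accumulates adverse events:

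- Sample size: "256 patients (128 per condition) would be necessary, including a possible dropout rate of 10" per cent, on the assumption that "the incidence of the primary endpoint with LAMS and DPPS is 90% and 75%, respectively".
- Outcomes and Table 2: adverse events are a secondary outcome. The listed categories include perforation, and bleeding that needs intervention, transfusion and observation in hospital.
- Statistical analysis plan: adverse-event incidence is to be compared between groups. The general level is given as: "Statistical analysis will be performed with two-sided tests at a level of significance of 0.05 (except where specified".
- Discussion: adverse-event incidence is part of the superiority question. The section also reports serious LAMS-related events in another randomised trial, including "delayed bleeding in 50% of patients (6/12"), and then says that the team's own centre experience found LAMS safe.

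**The concern.** The rule is triggered by a single event. It does not depend on which stent the patient received, whether the event is attributed to the stent, or how many patients have been treated. One event cannot separate device harm from the course of a severe underlying disease, and it cannot show which stent is safer. Yet it would end a trial that lists such events among its outcomes and intends to compare them.

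If the rule is followed, the trial probably stops short of its size and the superiority question is answered with too little power. If it is not followed, the real stopping decision in an open-label trial is made outside the written protocol.

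A smaller question attaches to the same paragraph. It says that data will be analysed at half-way but not whether clinical success is compared then, and neither the sample size nor the final significance level mentions the look.

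**Working it through.** **Step 1. The plan's own sample size.** Inputs (Sample size section): success 90% and 75%, so the mean is 0.825; one-sided alpha 0.025 (quantile 1.960); power 85% (quantile 1.036); dropout 10%.

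n = [1.960·√(2·0.825·0.175) + 1.036·√(0.90·0.10 + 0.75·0.25)]² / 0.15² = 113.7, so 114 per arm. Dividing by 0.9 gives 127 per arm, or 254 in total, against 256 stated. The figure reproduces to within two patients as a single-look design.

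**Step 2. Chance that the rule is triggered.** With per-patient risk p and independent patients, P(at least one serious event among m patients) = 1 − (1 − p)^m. The article gives no p for this trial, so p is an assumed range. Half-way is m = 128; the full trial is m = 256.

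| Assumed p | By 128 patients | By 256 patients |
|---|---|---|
| 0.5% | 47% | 72% |
| 1% | 72% | 92% |
| 2% | 92% | 99.4% |
| 5% | 99.9% | about 100% |

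A 95% chance of triggering needs p of about 2.3% by 128 patients, or 1.2% by 256.

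The only rate in the article is 6/12 for delayed bleeding with LAMS elsewhere. Its exact 95% interval is 21% to 79%. At 1:1 allocation, half-way has 64 LAMS patients. Even at the lower limit, 1 − (1 − 0.211)^64 exceeds 99.999%. This illustrates the conflict with the article's own citation; it is not a forecast for this trial.

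**Step 3. Two readings of the sentence.** It may apply only at the interim, or at any time.

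- Interim only: the 128 column applies and the trial stops at about half size.
- Any time: the 256 column applies, and the stop comes at the first event. On average that is patient 1/p, so about patient 20 at 5%.

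**Step 4. Power after a stop at half-way.** There are 64 per arm; 64 × 0.9 = 57.6, so 57 evaluable. With the plan's formula, z = [0.15·√57 − 1.960·√(2·0.825·0.175)] / √(0.90·0.10 + 0.75·0.25) = (1.132 − 1.053)/0.527 = 0.15, which gives power of about 56%. This is an upper figure: the look is triggered by enrolment, so some one-month outcomes would still be pending. An earlier stop leaves less.

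**Step 5. Significance level (conditional).** If the look can stop the trial only for safety, the efficacy error of the final test is not inflated. If clinical success were also tested there at two-sided 0.05 with a possible stop, two looks at |z| > 1.96 with half the information at the first (correlation √0.5) give an overall error of 0.083. O'Brien-Fleming levels of 0.0052 and 0.0480 would hold 0.05.

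**The case against.** Three objections carry weight.

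First, a reader might infer that early termination is almost certain. The documents do not support that without qualification. They give no serious-event rate for this trial and none for DPPS. The 6/12 comes from 12 patients elsewhere, and the Discussion adds that the team found LAMS safe at its own centre, without a rate. At 0.5% to 1% the chance by half-way is 47% to 72%. This limits the wording. It does not rescue a rule that a single event can trigger.

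Second, a reader might infer that the look leaves the final 0.05 test unprotected. The article does not show this. It names no efficacy test and no efficacy stop at half-way. The only stated consequence is a safety stop, which does not inflate the efficacy error. The 0.05 carries an exception clause, and boundaries are commonly placed in an analysis plan, which is not shown. What stands is that the purpose of the look is unclear.

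Third, it might be said that stopping criteria belong in the full protocol. That would answer a silence. Here the article states an unconditional rule, and the rule disagrees with its other sections.

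Central CT reading and a blinded statistician are stated safeguards, but they do not bear on the termination rule.

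**Conclusion.** The point holds for the termination rule. As written, it is inconsistent with the sample size, with the planned comparison of adverse events and with the serious events the article cites, and it must be put right. Its size depends on an assumed serious-event rate: at 2% or more the rule is triggered with at least 92% probability by half-way, while at 0.5% the figure is 47% by half-way and 72% by full enrolment. A stop at half-way leaves at most about 56% power under the plan's own success rates and 10% dropout, against 85%. That is a serious loss, but it does not mean that no result could be reached.

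The significance-level point is secondary and conditional. The 8.3% applies only if clinical success is tested at half-way at an unadjusted 0.05 with a possible stop, which the article does not say is planned.

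**What to change.** Reconcile the Outcomes, Sample size, Data management, Statistical analysis plan and Discussion sections on termination, so that the written rule fits the events the trial expects and plans to compare. The text should also say whether the rule applies throughout or only at the interim. The criterion itself is for the sponsor's safety reviewers; no particular safety boundary or between-arm comparison is proposed here.

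Add one sentence on the purpose of the half-way look. If it is for safety only, say so, and the final two-sided 0.05 stands. If clinical success is to be tested with a possible stop, specify group-sequential bounds, for example O'Brien-Fleming at 0.0052 and 0.0480.

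The cost is a wording amendment with no added patients. If bounds were adopted, the approximate power of the final test alone at 114 per arm would go from 85.1% to 84.7%.
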